### Sample size

The sample size was calculated using G*Power software (version 3.1) for a repeated-measures ANOVA (within-between interaction) to detect changes in DKV angle at initial contact. The effect size was derived from the group × time interaction reported for DKV at initial contact in a previous neuromuscular training study with dual cognitive tasks [24] (partial η² = 0.19), converted to an effect size f = 0.48. Based on a significance level (α) of 0.05, statistical power (1-β) of 0.95, and an assumed correlation of r = 0.5 between repeated measures, a minimum total of 18 participants was required. The required sample size was initially determined based on the primary outcome measure (the DKV angle) to ensure sufficient statistical power. To adjust for multiple secondary outcome assessments and an estimated 20% attrition rate, we inflated the target enrollment to 30 participants, who will be randomly allocated in a 1:1 ratio to the intervention and control groups.

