### Statistical methods

Descriptive statistics, including means and standard deviations, will summarize the data. The Shapiro-Wilk test will assess data normality. Baseline characteristics will be summarized descriptively between groups. Repeated-measures ANOVA will be used to evaluate the group × time interaction effect as the primary indicator of intervention effectiveness (training vs. control; pre-test vs. post-test). Pairwise comparisons following significant interactions will be conducted with Bonferroni correction to control type I error. The five secondary outcome domains (cortical brain activity, lower-limb muscle activation, single-leg balance, muscle strength, and knee joint proprioception) will be interpreted as exploratory outcomes and hypothesis-generating findings. Partial eta squared will quantify effect sizes, interpreted as small (0.01), medium (0.06), or large (0.14). All analyses will be performed using SPSS version 27 with α = 0.05 and a 95% confidence level.

Given the modest sample size, supplementary analyses will be conducted. Baseline values will be reviewed descriptively, and if clinically meaningful baseline imbalance is observed, ANCOVA models adjusting for baseline values will be performed as sensitivity analyses. Missing data patterns will be assessed, and linear mixed models with appropriate covariance structures will be considered as sensitivity analyses to evaluate robustness under missing-at-random assumptions. Any meaningful discrepancy between supplementary analyses and the primary ANOVA will be reported and discussed.

To assess clinical significance and intervention effectiveness, minimal clinically important difference (MCID) and minimal detectable change (MDC) will be calculated at a 95% confidence level. The MDC will be derived using the standard error of measurement (SEM), as defined by the following formulas [28]:

$$\begin{array}{c} \text{SEM }=\;{\text{SD}}_{\text{pre}}\;\times \;\sqrt{(\text{1}-\text{ ICC})\;} \end{array}$$

$$\begin{array}{c} {\text{MDC}}_{\%\text{9}\text{5}}\;=\;\text{1}.\text{96 }\times \sqrt{\text{2}\;\times \text{ SEM}} \end{array}$$

$$\begin{array}{c} {\text{MCID}}_{\text{RCI}}=\;\text{1}.\text{96 }\times \;{\text{SD}}_{\text{pre}}\;[\sqrt{\left(\text{2}\times (\text{1}-\text{ICC})\right)}] \end{array}$$

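### The stated 95% power rests on applying G*Power's repeated-measures factor of 4 to an effect size that already contains it; for the cited effect, power is about 58–62% with the 24 completers expected

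*Protocol article*

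**What the plan says.** The Sample size section of the protocol article gives a complete specification. The software and test are stated: "The sample size was calculated using G*Power software (version 3.1) for a repeated-measures ANOVA (within-between interaction"). So is the origin of the effect: "The effect size was derived from the group × time interaction reported for DKV at initial contact", in an earlier dual-task training study, with the conversion "partial η² = 0.19), converted to an effect size f = 0.48". The error rates follow: "Based on a significance level (α) of 0.05, statistical power (1-β) of 0.95". The result is: "an assumed correlation of r = 0.5 between repeated measures, a minimum total of 18 participants was required". Enrolment is then raised to 30 to allow for 20% attrition and for the secondary outcomes, with participants "randomly allocated in a 1:1 ratio to the intervention and control groups".

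The Statistical methods section makes the same effect the primary test, with two groups and two time points: "group × time interaction effect as the primary indicator of intervention effectiveness (training vs. control; pre-test vs. post-test"). The G*Power effect-size option is not named.

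**The concern.** For a group × time interaction, partial eta-squared is SS(interaction) / [SS(interaction) + SS(within-subject error)]. With two time points, that error term is the variability of the change scores. The gain from measuring each player twice, and from the pre/post correlation, is therefore already in the figure of 0.19 and in the f derived from it.

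G*Power's default option for this module expects a different f, one scaled to the standard deviation of a single measurement. It then supplies the repeated-measures gain itself through the number of measurements and the correlation entered. If an f from an interaction partial eta-squared is entered there, the gain is counted again.

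At stake is the power claim on which a reader would judge an inconclusive result. The comparator is active and receives the same exercises, so a null result is a real possibility. How far it speaks against the cognitive component depends on the power the trial actually had.

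**Working it through.** **Inputs.** From Sample size: partial eta-squared 0.19, f = 0.48, alpha 0.05, target power 0.95, r = 0.5, N = 18, 30 enrolled, 20% attrition. From Statistical methods: 2 groups and m = 2 times. Expected completers: 30 × 0.8 = 24.

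**Conversion.** f = √(0.19/0.81) = 0.484, which the plan gives as 0.48. The conversion is right.

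**Reproducing N = 18.** Power comes from the noncentral F distribution with 1 and N − 2 degrees of freedom. Under the G*Power default,

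λ = f² · N · m/(1−r) = f² · N · 2/0.5 = 4 f² N.

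With f = 0.48:
- N = 16: λ = 14.75, power 0.946
- N = 18: λ = 16.59, power 0.968

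The smallest even N that reaches 0.95 is 18, an exact match. Under the 'as in SPSS' option the answer would have been 60–62, so the stated N identifies the option used.

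**What effect that run assumes.** With equal arms, the difference in mean change, in SDs of change, is d = 2√(λ/N).
- Default run: d = 2√(4f²) = 4 × 0.48 = 1.92. Partial eta-squared = 4f²/(1 + 4f²) = 0.9216/1.9216 = 0.48.
- Cited effect: d = 2 × 0.484 = 0.97. Partial eta-squared = 0.19.

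The planned difference is about twice the one cited.

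**Power for the cited effect.** Two conventions are in use once the surplus factor is removed: λ = f²(N−2), which is the 'as in SPSS' option, and λ = f²N. Each range covers f = 0.48 to 0.484.

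| N | Default, λ = 4f²N (f = 0.48) | λ = f²(N−2) | λ = f²N |
|---|---|---|---|
| 18 | 96.8% | 43.8–44.5% | 48.2–48.9% |
| 24 | 99.4% | 57.6–58.4% | 61.3–62.1% |
| 30 | 99.9% | 68.9–69.6% | 71.8–72.6% |

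A simulated two-sample t test on change scores with d = 0.97 gave 49%, 62% and 72% at N = 18, 24 and 30, in line with λ = f²N.

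**Sample size for the cited effect** (even totals): 95% power needs 60–62 under λ = f²(N−2) and 58–60 under λ = f²N. Power of 80% needs 36–38 across both conventions.

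**Source of the factor 4.** Half is the number of measurements (m = 2) and half is 1/(1−r) = 2. With r = 0 under the default option, λ = 2f²N and power at N = 18 would still show as 77%.

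**Detectable effect at 80% power.** The λ required is 8.59 at N = 24 and 8.42 at N = 30.
- N = 24: d = 2√(8.59/24) = 1.20. Partial eta-squared is 8.59/(8.59 + 22) = 0.28 under λ = f²(N−2), or 8.59/(8.59 + 24) = 0.26 under λ = f²N.
- N = 30: d = 2√(8.42/30) = 1.06. Partial eta-squared is 8.42/(8.42 + 28) = 0.23, or 8.42/(8.42 + 30) = 0.22.

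**The case against.** **The trial will not analyse 18.** The plan calls 18 a minimum and enrols 30, more than the 18/0.8 = 22.5 that attrition alone would require. This stands: a reader might infer that the trial has 44% power, but the documents do not support that as its operating figure. The relevant range is 24 to 30 analysed. The larger enrolment narrows the gap but does not close it, since full retention gives only 69–73%.

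**The correlation is not the whole mechanism.** A reader might infer that r = 0.5 alone was counted twice. It accounts for one factor of 2 out of 4; the other comes from the number of measurements. Setting r = 0 under the default option would not correct the calculation.

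**No single corrected percentage is the true one.** The two conventions differ by up to about 4 percentage points at these sizes, so ranges are the fair statement.

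**The cited study is not available.** The plan does not give its number of groups, time points or covariates. This is a real limit on the exact percentages. The plan does describe the figure as a group × time interaction effect, and any such partial eta-squared is scaled to within-subject error.

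**The arithmetic is right.** Both the conversion to f and the N of 18 reproduce. The fault is that the effect size does not fit the option it was entered under. The package named for the trial's own analysis says nothing about that option; only the stated N does.

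**A misread null result is not certain.** The plan acknowledges a modest sample and will report effect sizes and sensitivity analyses. That softens the consequence but leaves the power statement incorrect.

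**Conclusion.** The point holds. The claim that 18 participants give 95% power for the cited effect is wrong as written. For an interaction partial eta-squared of 0.19, power is about 44–49% at 18, 58–62% at the 24 completers expected and 69–73% with all 30. About 58–62 participants in total would be needed for 95%. The calculation behind the stated figure corresponds to a partial eta-squared of about 0.48.

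This assumes that the cited 0.19 comes from an ordinary two-group, two-time interaction test, as the Sample size section implies, and that 20% attrition leaves 24. It also infers the default G*Power option from the stated N, which that option reproduces exactly. A reader might go further and conclude that the trial must double its enrolment. That does not follow: a trial of 30 can be justified on feasibility, provided its power or detectable effect is stated correctly.

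**What to change.** Rerun the calculation with G*Power's 'as in SPSS' effect-size option, which does not apply m/(1−r) again, and name the option in the text. Then do one of the following:

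- Replace the 95% power and minimum-18 statements with the power for the cited effect: about 58% with 24 completers and 69–70% with 30 under that option.
- Keep N = 30 and state the effect detectable with 80% power: a between-arm difference of about 1.20 SD of change with 24 completers, or 1.06 SD with 30. As entered under the 'as in SPSS' option, these are partial eta-squared values of about 0.28 and 0.23; under λ = f²N they are 0.26 and 0.22. Say which convention is used, so that the figures can be reproduced.

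In either case, state that the cited 0.19 is taken to be from a two-group, two-time interaction test, after checking this against the source.

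The cost is one reworded paragraph and a less favourable power statement. Enrolment and the planned analysis do not change.

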### Assignment of interventions: Allocation

#### Sequence generation.

Participants will be randomized using a computer-generated random number sequence. They will be allocated to either the intervention or control group in a 1:1 ratio. To ensure group balance and minimize assignment predictability, block randomization with variable block sizes (for example, 4 and 6) will be employed. An independent researcher, not involved in recruitment, data collection, or intervention delivery, will generate the randomization sequence before the study begins.

### Concealment mechanism

To conceal allocation and prevent selection bias, the randomization sequence will be sealed in opaque, tamper-proof, sequentially numbered envelopes. Each envelope will contain a card indicating group assignment corresponding to the participant’s number. The envelopes will be opened only after completion of baseline assessments. An independent individual, not involved in study implementation, will prepare and manage the envelopes.

### Implementation

An independent investigator, not involved in participant recruitment, assessment, or intervention administration, will generate the randomization sequence and maintain exclusive access to the randomization list. After confirming eligibility and obtaining informed consent, this investigator will randomize participants. The study coordinator, blinded to group assignment, will enroll eligible female volleyball athletes with DKV and schedule assessments. Due to the nature of the intervention, trainers cannot be blinded to group allocation. The allocation process is designed to minimize selection and performance bias throughout the study.

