### Maintenance strategy

Several strategies will be used to minimize participant dropout. A study coordinator will send reminder text messages before each scheduled training and assessment session. Training sessions will be embedded within each team’s existing practice schedule to minimize scheduling conflicts with competitions and academic commitments. Where feasible, makeup sessions will be offered for absences due to illness or minor scheduling conflicts, provided the participant does not meet the withdrawal threshold defined in the Exclusion Criteria. Reasons for dropout or withdrawal will be systematically recorded and reported using a CONSORT flow diagram. Participants who complete the full protocol will receive individualized feedback on their landing mechanics as a non-monetary incentive to continue engaging.

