### Qualifications of intervention providers

The intervention will be overseen by a PhD-level sports rehabilitation specialist with expertise in sports training, who will explain the study’s objectives to coaches and athletes, obtain informed consent, and supervise all assessments in the Sports Rehabilitation Laboratory at Bu-Ali Sina University. Day-to-day implementation of the training program will be conducted by trained team coaches under the supervision of the research team.

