Athletes will progress to the next training phase only when they consistently meet predefined progression criteria across three consecutive sessions. Movement quality will be assessed by a trained coach using a standardized checklist, ensuring appropriate lower-extremity alignment according to predefined movement-quality criteria. Cognitive performance will also be evaluated, requiring athletes to commit no more than three predefined cognitive errors per session during tasks involving stimulus responses or rule-based challenges. Athletes must maintain movement quality under dual-task conditions without clinically meaningful deterioration compared with single-task performance and execute tasks at the prescribed speed and intensity while meeting cognitive demands. Since progression is individualized, athletes who do not meet the criteria after completing the planned two-week phase will remain at the same level with modified or alternative exercises of similar complexity until the requirements are achieved, thereby supporting adequate motor learning, confidence development, and minimizing inappropriate progression-related injury risk. All progression decisions will be documented using standardized forms and reviewed weekly by the supervising sports rehabilitation specialist to ensure safety.

Training intensity will be indirectly quantified using the session rating of perceived exertion (session-RPE) method [23]. Approximately 30 minutes after each session, each participant will rate her perceived exertion using the modified Borg CR-10 scale; session-RPE will then be multiplied by session duration (minutes) to calculate session training load. Weekly training load will be reviewed by the supervising sports rehabilitation specialist alongside the movement-quality and cognitive-error checklists to identify unusual increases in perceived exertion and inform individualized progression decisions.

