### Assignment of interventions: Blinding

This study will be conducted as a participant- and assessor-blinded randomized controlled trial. Participants will be informed that they are receiving training, but will not know whether the program includes neuromuscular training with or without cognitive components. Given the structural similarity between protocols, participants may be unlikely to determine their group assignment. To minimize communication between groups, intervention and control sessions will be scheduled on separate training days. Outcome assessors will remain blinded to group assignments. Participants will be instructed not to disclose intervention-related information during evaluations.

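### The coordinator declared blinded appears also to send reminders for arm-specific training days, and the specialist overseeing the intervention supervises all assessments, so the stated blinding cannot hold once training starts

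*Protocol article*

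**What the plan says.** All references are to the protocol article.

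- **Implementation:** "The study coordinator, blinded to group assignment, will enroll eligible female volleyball athletes with DKV and schedule assessments". An independent investigator alone holds the list and randomizes after eligibility and consent.
- **Maintenance strategy:** "A study coordinator will send reminder text messages before each scheduled training and assessment session".
- **Assignment of interventions: Blinding:** to limit contact between the arms, "intervention and control sessions will be scheduled on separate training days". The same section calls the trial participant- and assessor-blinded.
- **Qualifications of intervention providers:** "The intervention will be overseen by a PhD-level sports rehabilitation specialist with expertise in sports training". The same specialist is to "obtain informed consent, and supervise all assessments in the Sports Rehabilitation Laboratory at Bu-Ali Sina University". Coaches run the daily training.
- **Intervention protocol:** progression decisions are recorded on forms and "reviewed weekly by the supervising sports rehabilitation specialist to ensure safety".
- **Sequence generation and Concealment mechanism:** "block randomization with variable block sizes (for example, 4 and 6) will be employed". Envelopes are opaque and numbered, are managed by someone outside the study, and are opened only after baseline assessments.
- **Timeline (Fig 1 caption):** enrolment and screening come first, then allocation and baseline, then the training periods.

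**The concern.** Two safeguards on which the trial relies are assigned to people whose other duties undo them.

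The first is the coordinator. A person who knows which athletes to text before which sessions knows how the athletes divide between the arms when the arms train on different days. The article relies on that person's blinding while she still schedules the post-tests.

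The second is the overseeing specialist. Someone who reviews progression each week, including the cognitive-error criteria, cannot be blind to arm. Yet the same role supervises the assessments, and the primary outcome is an angle read from two-dimensional video.

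There is also a conditional risk. If athletes were allocated one by one while others were still being enrolled, staff who knew the running tally could guess the next assignment in a small block. Selection bias could then enter before baseline. How much weight this deserves depends on the order of enrolment and allocation.

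**Working it through.** **1. Coordinator.** The section texts combine as follows.

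| Section | Statement | Consequence |
|---|---|---|
| Implementation | Coordinator is blinded, enrols, schedules assessments | Must not learn who is in which arm |
| Maintenance strategy | A coordinator texts before each training session | Holds each athlete's session dates |
| Blinding | Arms train on separate days | Session date separates the arms |

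The Intervention protocol section gives 3 sessions a week for 8 weeks, so 3 × 8 = 24 sessions per athlete. The reminder list sorts the athletes into two sets from the first training week. The three statements cannot all be true of one person.

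**2. Specialist.** Oversight of the intervention and supervision of all assessments are given to one role in one sentence. Weekly review of progression is given to the supervising sports rehabilitation specialist. At post-test that role has eight weeks of arm-specific information.

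**3. Could the next allocation be guessed?** The plan gives no figure for this, so there is none to reproduce. Inputs: "we inflated the target enrollment to 30 participants, who will be randomly allocated in a 1:1 ratio", and the example block sizes 4 and 6, assumed equally likely. The guesser always names the arm that is behind and tosses a coin when the arms are level.

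Suppose every earlier allocation is known at once. The expected number of correct guesses per block, position by position, is:

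- Block of 4: 1/2 + 2/3 + 2/3 + 1 = 2.833, and 2.833/4 = 0.708.
- Block of 6: 0.5 + 0.6 + 0.6 + 0.7 + 0.7 + 1 = 4.1, and 4.1/6 = 0.683.
- Equal mix: (2.833 + 4.1)/(4 + 6) = 0.693.

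Simulation of sequences cut at 30 athletes gives 0.688, slightly lower because the last block is often incomplete. About 6% of assignments are certain if the guesser must infer each block's size, and about 27% if each block's size is known.

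When the most recent allocations are not yet visible, the advantage falls quickly (same simulation):

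| Most recent allocations not yet seen | Correct guesses |
|---|---|
| 0 | 69% |
| 1 | 59% |
| 2 | 55% |
| 3 | 52% |
| 4 | 51% |
| 6 or more | 50% |

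Reminders begin only with training, and the Outcomes section sets the pre-test 72 hours before training starts. If 30 athletes were enrolled evenly over 30 days (an assumption), 72 hours would correspond to about 3 athletes, so the reminder route would give about 52%. If all athletes are enrolled before the first envelope is opened, the figure is 50%.

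**4. Illustrative bias under the worst case.** One arm is behind at 60.9% of assignments, and the guess is then right 80.8% of the time. If each guess shifts the enrolled athlete's prognosis by d towards the favoured arm, the between-arm difference is about 2 × 0.609 × (0.808 − 0.192) × d = 0.75d. With d = 0.1 SD this is about 0.08 SD, and with d = 0.2 SD about 0.15 SD. The documents give no value for d.

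**The case against.** A reader might infer that earlier allocations are visible at enrolment, so that concealment fails. The documents do not support that. No section says enrolment continues after the first envelope is opened. Fig 1 puts enrolment and screening before allocation, and allocation before training. The month in the Recruitment section covers recruitment and screening, not allocation. An athlete's reminders start only after her own consent, baseline and allocation. Paired exercises within team practice also suggest a common start. That the article does not spell out when enrolment closes is not an error in a condensed text. This objection stands, and it limits prediction to a conditional remark. The order is not beyond doubt, since Fig 1 speaks of an enrolment week while Recruitment allows a month, but doubt is not evidence of rolling allocation.

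Other points carry some weight:

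- The reminder-sender is called a study coordinator in one section and the study coordinator in another, so identity is likely but not stated. If two people are meant, the text should say so.
- Sorting athletes into two sets does not by itself reveal which set has the cognitive tasks. That softens the breach, but knowing group membership is already incompatible with the declared blinding.
- Scheduling or supervising an assessment is not scoring it. The Blinding section separately requires blinded outcome assessors, and Data management gives data collection to two trained specialists. This limits the likely harm, but the overseeing specialist is still placed over every assessment.
- An independent list-holder, opaque envelopes and variable blocks are sound safeguards. The block sizes are only an example, and naming them is a reporting preference rather than a fault.

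**Conclusion.** The contradiction in roles is real and follows from the text alone. The coordinator's declared blinding cannot hold once training starts if that person sends the training reminders. The person overseeing the intervention should not also supervise assessments in a trial described as assessor-blinded. The first conclusion assumes that both coordinator references mean one person, which is the natural reading.

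Failure of allocation concealment is not established. Under the order that Fig 1 suggests, correct guessing stays at 50%. Under rolling allocation it would range from 50% to 69%, and the upper end needs immediate sight of every earlier allocation. The figures of 0.08 to 0.15 SD rest on that worst case and on assumed shifts in prognosis, so they should not be cited as the expected bias.

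**What to change.** 1. **Maintenance strategy:** have the coaches, who are already unblinded, send the training reminders. The coordinator sends assessment reminders only and has no access to the training-day lists.
2. **Concealment mechanism and Implementation:** state that no envelope is opened until eligibility, consent and baseline are complete for all athletes. This makes the order in Fig 1 explicit and removes any route to predicting assignments. It also makes it harmless for concealment that the overseeing specialist obtains consent.
3. **Qualifications of intervention providers:** reconcile the roles using existing staff, so that the person overseeing the intervention does not supervise the post-test assessments.

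These are changes of wording and of duties, with no added athletes or staff. The downside is that athletes screened early wait up to the one-month recruitment period before allocation, and coaches take on the reminders.
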